## Abstract

**Background:**

Transitioning to residential centers often induces significant psychological stress in older adults, adversely affecting their psychological well-being (PWB) and ability to age healthily. Chinese art activities and their combination with peer group participation have demonstrated efficacy in improving emotional well-being and fostering social connectivity among younger populations but have not been examined in older adult populations to date.

**Objective:**

This study aims to assess the efficacy of Chinese art activities or their combination with peer group participation in enhancing PWB among Chinese older adults living in a residential center.

**Methods:**

This multicenter randomized, assessor- and analyst-blinded trial uses a “max-min-con” design with 3 groups: control, Chinese art activities, and Chinese art activities plus peer group participation (1:1:1 allocation). A total of 90 participants aged 60 to 85 years and with a stay of 1 year or less will be recruited from 3 older adult centers (30 from each center) and assigned via minimized randomization to the groups. Interventions will consist of 3 sessions within a single week (Monday, Wednesday, and Friday). Baseline evaluations will be conducted before randomization to assess PWB, loneliness, happiness, relaxation, and salivary cortisol levels. Outcome evaluations will be conducted 30 minutes prior to and following each intervention session to assess immediate effects. A follow-up evaluation is planned 1 week after the final intervention to measure sustained outcomes.

**Results:**

The study was funded in September 2024. Participant recruitment commenced on May 9, 2025, and ended on August 20, 2025, with the recruitment of 90 participants. Data collection ended on October 31, 2025, and data analysis is expected to conclude in April 2026, with the anticipated publication of results in 2026.

**Conclusions:**

This study is the first randomized controlled trial to evaluate the effects of Chinese art activities, either alone or combined with peer group participation, on enhancing PWB in older people and the efficacy of salivary cortisol as a biomarker for the assessment of PWB. The findings will provide empirical evidence to assist policymakers and older adult centers in selecting appropriate interventions, with the long-term potential to improve psychological health in older adults.

## Introduction

### Background

The global older adult population is growing rapidly, posing significant social and economic future challenges. In China, the 1-child policy has exacerbated older adult care difficulties, increasing reliance on institutional care. However, transitioning to older adult centers often induces stress [1-3]; reduces psychological well-being (PWB); and can cause physical symptoms such as insomnia and appetite loss [4], which lead to worsened health [5]. In China, which has historically relied on home-based care, relocation to older adult centers can heighten feelings of neglect and embarrassment [3], further compromising PWB.

Maladaptation in older adults is more likely to occur in the first year of entry to older adult centers as they face the loss of familiar surroundings and must adapt to a new environment [6]. These phenomena may be of heightened concern in Chinese culture, where traditional values of filial piety emphasize children caring for their older parents. The admission to older adult centers for older adults may lead to feelings of abandonment and shame. Consequently, a decline in PWB is more common among new residents, especially in the Chinese context [7,8]. Therefore, researching ways to improve the PWB of new residents is highly meaningful.

Recent studies have explored behavioral interventions such as happiness therapy [9,10], life review therapy [11,12], and cognitive behavioral therapy [13-15] to improve PWB. A limitation of these interventions is that they are often perceived as uninteresting, which may promote disengagement among older adults [16]. Additionally, many interventions primarily target younger adult populations, further limiting their applicability [17-20]. Another significant drawback is that these studies often rely solely on subjective data, lacking support from objective measurements, which may affect the validity and reliability of the findings [21-24]. Therefore, it is essential to develop practical, effective, and easily accepted interventions specifically designed to improve PWB among older adults while incorporating both subjective and objective data to ensure more robust and comprehensive results.

Art activities and group-based interventions are widely recognized as effective methods for enhancing PWB [25,26]. Some studies [27-30] have incorporated group discussions or supplementary activities into art-based interventions to improve outcomes. While these combined interventions have potentially shown some effectiveness, this benefit comes with the drawback of a longer duration, which may inadvertently introduce negative effects such as participant fatigue or reduced adherence [31]. Therefore, it is critical to examine whether art activities alone or in combination with group discussions are more effective in boosting PWB among new residents in Chinese older adult care centers.

### Conceptual Framework

The study is based on aesthetic theory and social support theory. Aesthetic theory underscores the significance of aesthetic experience in enhancing well-being via emotional and sensory reactions to art [32,33]. Interaction with beauty is correlated with favorable emotional states, which neuroscience links to the release of neurotransmitters such as endorphins and serotonin as well as a decrease in stress-related indicators, including cortisol [34-37]. Social support theory emphasizes that interpersonal interactions mitigate stress and improve well-being by providing emotional, informational, and companionship support [38-42]. Aesthetic theory corresponds to the creative process of Chinese painting and calligraphy in the Chinese art activity component of this intervention, mainly supporting the mechanisms of changes in emotional states and self-esteem levels. Social support theory corresponds to the peer group participation component, mainly guiding the mechanism of changes in perceived social support and loneliness. The concept structure of this study is shown in Figure 1.

This study is an exploratory trial. PWB, happiness, relaxation, loneliness, and salivary cortisol levels were selected as the dependent variables. Happiness, relaxation, and loneliness are all operationally defined as an immediate, subjective, and transient affective state characterized by momentary feelings [43,44]. Usually, PWB requires intervention for a longer period to manifest changes. However, as an exploratory trial, we still included it as an exploratory outcome measure to provide preliminary data for future research.

**Figure 1. F1:**
[figure not shown]
Conceptual framework of the study. PWB: psychological well-being.

### Objectives

The objectives of the trial are to establish whether (1) new residents in Chinese older adult centers have higher PWB scores, happiness, and relaxation, as well as lower levels of loneliness and salivary cortisol, after engaging in Chinese art activities; (2) new residents in Chinese older adult centers have higher PWB scores, happiness, and relaxation, as well as lower levels of loneliness and salivary cortisol, after engaging in Chinese art activities and peer group participation; (3) new residents in Chinese older adult centers engaging in a Chinese art activity and peer group participation intervention have higher PWB scores, happiness, and relaxation, as well as lower levels of loneliness and salivary cortisol, than those who only engage in Chinese art activities; and (4) salivary cortisol can serve as a biomarker reflecting changes in PWB and relaxation.

On the basis of aesthetic theory and social support theory, we propose the following hypotheses: (1) for objectives 1 and 2, we hypothesize that both Chinese art activities and Chinese art activities with peer group participation will promote PWB, happiness, and relaxation and alleviate loneliness; (2) for objective 3, we hypothesize that peer group participation will have a stronger effect than Chinese art activities; and (3) for objective 4, we hypothesize that salivary cortisol will be a biological indicator of PWB and relaxation.

## Methods

### Pilot Study

Prior to the trial, we conducted a pilot study with 20 older adults (10 per group) recruited from an older adult center in Suzhou that is not affiliated with the authors’ institutions in December 2024. The objectives were to assess feasibility and acceptability and refine intervention protocols. Recruitment achieved 100% of the target within 2 weeks. A total of 95% (19/20) of the participants attended all 3 sessions, with 1 dropout due to a spontaneous family trip. All assessment instruments were completed without missing data, and the saliva collection procedure was well tolerated (no refusals). Participants reported that the activities were enjoyable and easy to follow.

On the basis of the findings of the pilot study, the following improvements were made to the main experiment. The intervention time from morning to afternoon was adjusted based on the suggestions and preferences of the participants. Due to the widespread feedback from participants (10/15, 66.7%) that the Chinese calligraphy activity was not completed in time, the duration of this stage was extended from 10 minutes to 15 minutes. We further simplified the painting template to address the difficulty of Chinese painting raised by participants. Guidance was also added to the peer volunteer training on managing quiet participants.

The revised protocol obtained official approval before its implementation in the main study.

### Trial Design

This multicenter randomized, assessor-blinded trial is structured according to the “max-min-con” principle [45,46]: maximizing experimental variance by ensuring that art activities and art activities with peer group participation are delivered consistently and distinctly from the control condition; minimizing error variance by using standardized protocols for art activities and art activities with peer group participation, trained research assistants (RAs), and reliable measurement instruments; and controlling extraneous variance through minimized randomization and blinding of outcome assessors.

This study has 3 intervention groups: group A (Chinese art activities), group B (Chinese art activities+peer group participation), and group C (regular care), with participants randomized at a 1:1:1 allocation ratio. The study will be conducted consecutively at 3 older adult centers. These 3 centers all belong to Suzhou Health and Elderly Care Industry Development Group Co, Ltd. After on-site inspection, it was determined that the inclusion criteria (affiliation, bed capacity, facilities, management support, and accessibility) were met to ensure feasibility and reasonable representativeness. Each center is treated as a randomization unit. Figure 2 delineates the implementation phase and the data collection procedures in the study. The intervention takes place over 3 sessions in a single week (Monday, Wednesday, and Friday). Baseline evaluations of PWB, loneliness, happiness, relaxation, and salivary cortisol levels are conducted before randomization.

**Figure 2. F2:**
[figure not shown]
The implementation phase and data collection procedures.

Outcome measures are gathered 30 minutes prior to and following each intervention session to assess immediate effects. A concluding follow-up assessment takes place 1 week after the final session to examine enduring outcomes. Figure 3 illustrates the research design within a single environment. The study protocol (version 1.0 dated March 2, 2026) complies with the SPIRIT (Standard Protocol Items: Recommendations for Interventional Trials) checklist (Table 1).

**Figure 3. F3:**
[figure not shown]
CONSORT (Consolidated Standards of Reporting Trials) flow diagram. CAA: Chinese art activities; DV: dependent variable; PGP: peer group participation; RC: routine care; VAS: visual analog scale.

**Table 1. T1:** SPIRIT (Standard Protocol Items: Recommendations for Interventional Trials) table with the schedule of enrollment, interventions, and assessments.

	Study period					
	Enrollment (T–1)	Allocation (T0)	Intervention session—Monday (T1)	Intervention session—Wednesday (T2)	Intervention session—Friday (T3)	Intervention session—following Monday (T4)
Enrollment						
Eligibility screening	✓					
Information sheet	✓					
General informed consent	✓					
Group-specific informed consent		✓				
Allocation		✓				
Interventions						
Usual care			✓	✓	✓	
Usual care+CAA^a^			✓	✓	✓	
Usual care+CAA+PGP^b^			✓	✓	✓	
Assessments						
PWB^c^ score	✓					✓
Loneliness score—VAS^d^	✓		✓^e^	✓^e^	✓^e^	✓
Happiness score—VAS			✓^e^	✓^e^	✓^e^	✓
Relaxation score—VAS			✓^e^	✓^e^	✓^e^	✓
Salivary cortisol level			✓^e^	✓^e^	✓^e^	✓

a CAA: Chinese art activities.

b PGP: peer group participation.

c PWB: psychological well-being.

d VAS: visual analog scale.

e This includes pretest and posttest assessment.

### Sample Size

The sample size of this randomized controlled trial (RCT) was calculated based on a previous study. The effect size used the formula [50].

In this formula, *d* is the effect size, μ1 is the mean of the intervention group, and μ2 is the mean of the control group.

$$\sigma =\sqrt{\text{SD}1^{2}+\text{SD}2^{2}}/2$$

Where SD₁ and SD₂ are the standard deviations of the control group and the intervention group, respectively. The term σ represents the pooled SD, calculated under the assumption that the two groups have equal sample sizes. This pooled SD is used to compute Cohen *d* effect size. The sample size calculation is based on the loneliness effect size (*d*=0.92) from the study by Aydın and Kutlu [51], which we selected as the most conservative among the 3 available effect sizes (the other 2 being happiness [*d*=2.66] and relaxation [*d*=2.32]) [52]. Using a power chart [53], the sample size was determined based on an effect size of 0.92, a power of 0.80, and an α level of .05. The analysis indicated that a minimum of 25 participants per group would be required. This study will recruit 90 individuals to account for a potential dropout rate of 20%. The trial is scheduled at 3 independent institutions, each having 3 groups with 10 participants per group.

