### Conclusions

This study will provide evidence-based support for incorporating Eastern wisdom into nursing practice. The development and implementation of culturally adapted art activity interventions for new residents of Chinese older adult centers has the potential to yield significant insights into the delivery and policies of aged care. The findings could inform the creation of practical guidelines for enhancing PWB in older adult centers by demonstrating the efficacy of culturally customized art-based interventions. The study emphasizes the significance of incorporating cultural traditions into contemporary care systems, presenting a scalable approach that may be applied to other aged care cultural contexts.

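### Psychological well-being (PWB) is the trial's stated aim in some sections and an exploratory outcome in another, and the only sample size basis is loneliness, so the plan supports no efficacy or no-effect conclusion on PWB

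*Protocol article*

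**What the plan says.** **Sizing.** In the Sample Size section, "The sample size calculation is based on the loneliness effect size", with d = 0.92, "which we selected as the most conservative among the 3 available effect sizes". The remaining two are named in brackets: "the other 2 being happiness" (2.66) and relaxation (2.32). Then "the sample size was determined based on an effect size of 0.92, a power of 0.80, and an α level of .05". The result is 25 per group; 90 are recruited (30 per group) to allow for 20% dropout. No effect size appears for PWB or for salivary cortisol.

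**PWB as the aim.** The abstract's Objective is to "assess the efficacy of Chinese art activities or their combination with peer group participation in enhancing PWB among Chinese older adults". The Objectives section lists PWB first in objectives 1 to 3 and hypothesizes that both programmes promote it. The closing Conclusions say: "The findings could inform the creation of practical guidelines for enhancing PWB in older adult centers".

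**PWB as exploratory.** The Conceptual Framework says: "Usually, PWB requires intervention for a longer period to manifest changes". It adds that, the trial being exploratory, "we still included it as an exploratory outcome measure to provide preliminary data for future research".

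**Analysis.** Statistical Methods lists PWB among five dependent variables. Its paired and independent t tests for objectives 1 to 3 name happiness, relaxation, loneliness and cortisol only. PWB enters only under objective 4, an ordered logistic regression of change in PWB or relaxation on cortisol. The paragraph then excludes any further analysis.

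**The concern.** An aim and an exploratory outcome carry different evidential weight, and the article assigns both roles to PWB. A reader of the abstract sees an efficacy trial on PWB. A reader of the Conceptual Framework sees an outcome kept for preliminary data, which the authors say usually needs longer than this intervention allows. The one power statement belongs to neither role: it concerns loneliness, one of three outcomes that the same section defines as momentary states.

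At stake is what may be concluded about PWB. If the status is left open, a PWB result could be presented as showing, or failing to show, efficacy, although no PWB effect was ever assumed and no group comparison of PWB is planned. Data collection is finished and analysis is due to conclude in April 2026, so the number of participants is fixed but the status of PWB can still be settled before results are reported.

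**Working it through.** **Inputs.** From Sample Size: d = 0.92 (loneliness), power 0.80, α = .05, 25 per group, 30 per group recruited, 20% dropout. Sidedness is stated only for the paired tests; two-sided is assumed here. The article gives neither a PWB effect nor a PWB SD, so PWB differences are in SD units and the effects tried are assumptions.

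**Step 1, the article's own figure.** Two-group formula: n = 2(1.960 + 0.842)²/d² = 15.70/0.8464 = 18.5, so 19 per group; the exact noncentral t solution is 19.55, so 20. The stated 25 is not reproduced for the planned t test, but it errs upward: at d = 0.92, power is about 0.89 with 25 per group. That is a separate matter. What counts here is the number available: 30 per group, or 30 × 0.80 = 24 after the stated dropout. At d = 0.92 these give power 0.94 and 0.88, so on the stated inputs loneliness is covered.

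**Step 2, detectable PWB difference.** This needs no assumed PWB effect. Two-sample t test, 2n − 2 degrees of freedom, noncentrality d√(n/2), solved for 80% power:

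- n = 24: d = 0.83 (0.826 × √12 = 2.86)
- n = 30: d = 0.74 (0.736 × √15 = 2.85)

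**Step 3, power at assumed PWB effects** (same test):

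| Assumed d | 24 per arm | 30 per arm | n per arm for 80% power |
|---|---|---|---|
| 0.2 | 10% | 12% | 394 |
| 0.3 | 17% | 21% | 176 |
| 0.5 | 40% | 48% | 64 |
| 0.8 | 77% | 86% | 26 |

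**Step 4, precision of a PWB estimate.** The half-width of a 95% CI for a difference of two means, in SD units, is t × √(2/n). For n = 24: 2.013 × 0.289 = 0.58. For n = 30: 2.002 × 0.258 = 0.52. An observed difference of zero would therefore leave differences of half an SD in either direction inside the interval.

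**Step 5, the roles of PWB side by side.**

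| Section | Role of PWB |
|---|---|
| Abstract, Objective | the outcome on which efficacy is assessed |
| Objectives | first-listed outcome of objectives 1 to 3, hypothesized to improve |
| Conceptual Framework | exploratory, usually slow to change |
| Sample Size | absent |
| Statistical Methods, objectives 1 to 3 | absent from the tests; further analyses excluded |
| Conclusions | basis for possible practice guidelines |

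The sizing and the tests fit the exploratory reading. The abstract, the objectives and the conclusions do not.

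**The case against.** The case for leaving the text alone has several parts.

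- **The phrase about being conservative.** A reader might infer that it is wrong because PWB and cortisol were left out. It is not: it is limited to three named effect sizes, and 0.92 is the smallest of them.
- **The power claim.** A reader might infer that 80% power is claimed for PWB. The article ties the 0.80 to d = 0.92 for loneliness and never extends it. Sizing on one outcome is ordinary, and an exploratory outcome needs no power.
- **Disclosure.** The Conceptual Framework states the status of PWB openly, Anticipated Findings speaks of exploratory work and preliminary evidence, and Limitations names the one-week duration. This lessens the harm, but it does not remove the conflict with the abstract, the objectives and the conclusions.
- **A false null or a chance positive.** A reader might expect a misleading PWB test. No between-group PWB test is planned that could produce one. That is a gap of its own: objectives 1 to 3 name PWB and the list of analyses, worded as closed, omits it.
- **Low power.** The figures at 0.2 to 0.5 SD show what would follow if effects were small, not that they are small. At 0.8 SD, power is 77% to 86%. Nor does the remark that PWB usually takes longer show that a null result is likely, or that PWB would move less than cortisol.

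All of this stands, and it narrows the point to the conflicting status of PWB and what may be concluded from it.

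**Conclusion.** The concern holds in this limited form. The article gives PWB two incompatible statuses, its only sizing is for loneliness at d = 0.92, and its group comparisons omit PWB. The Sample Size section contains no false statement on this point, but nothing in it supports an efficacy or no-effect conclusion on PWB.

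The firm figure is the detectable difference: about 0.83 SD with 24 per arm and 0.74 SD with 30, for 80% power. It assumes a two-sided .05 pairwise t test, no baseline adjustment (none is planned) and no multiplicity correction. Power at particular PWB effects rests on assumption alone. Salivary cortisol also lacks a sizing basis, but it is at least included in the planned tests. The point is worth correcting before results are reported; it does not call for a larger trial.

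**What to change.** 1. **Sample Size:** state that the 0.80 power refers to one pairwise loneliness comparison at d = 0.92 and does not extend to PWB or cortisol. Add that 24 to 30 per arm has 80% power only for a PWB difference of about 0.83 to 0.74 SD (two-sided .05 t test).
2. **Abstract Objective, Objectives, Anticipated Findings and Conclusions:** give PWB the exploratory status it has in the Conceptual Framework.
3. **Statistical Methods:** add a between-group PWB estimate with a 95% CI, labelled exploratory, with no efficacy or no-effect conclusion drawn from it. Amend the sentence that excludes further analyses, and date the change so that readers can see it came after data collection.
4. **Do not** move the efficacy objective to loneliness or another momentary outcome. Changing the aim after data collection has ended would create a worse problem than the one being repaired.

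Cost: wording, one added descriptive analysis, and the ethics board submission that the article promises for any modification. No more participants are needed. The downside is a weaker headline claim on PWB.

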For the testing of objectives 1 and 2, a dual test of intra- and intergroup comparisons will be used. If the data are normally distributed, 2-tailed paired-sample *t* tests will be used for intragroup comparison of the Chinese art activities group or the Chinese art activities and peer group participation group. This will test the intervention effects of the Chinese art activities or Chinese art activities with peer group participation interventions on happiness, relaxation, loneliness, and salivary cortisol levels before and after the intervention (3 times). We will use independent-sample *t* tests to compare the effects of the Chinese art activities or Chinese art activities with peer group participation interventions on happiness, relaxation, loneliness, and salivary cortisol levels with the control group. For the testing of objective 3, an independent-sample *t* test will be used to compare the effects of the Chinese art activities with peer group participation and the Chinese art activities interventions on happiness, relaxation, loneliness, and salivary cortisol levels. For the testing of objective 4, salivary cortisol levels will be the main independent variable, and changes in PWB or relaxation will be divided into 3 quartiles as dependent variables. Ordered logistic regression analysis will be used to explore the association between salivary cortisol and these 2 variables. There will be no additional analyses.

Due to the harmless and short-term nature of this study, there will be very little missing data. Preliminary analysis will be conducted based on the complete case. We will use mean imputation for any missing data within a scale. Following the intention-to-treat principle, participants with intervention data will be included in the analysis.

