## Discussion

### Anticipated Findings

To our knowledge, this is the first exploratory study on the improvement effect of traditional Chinese art activities on PWB among individuals who are new residents of older adult centers. On the basis of our pilot study demonstrating the feasibility and potential of Chinese art activities and Chinese art activities with peer group participation, this multicenter RCT aims to provide preliminary evidence on the effectiveness of these interventions in institutional environments. By comparing the outcomes of both interventions, we expect to determine the best program that is suitable for individuals who are new residents of older adult centers. At the same time, we speculate that combining subjective scales with the objective indicator of salivary cortisol can effectively verify the positive effects of Chinese art activities and Chinese art activities with peer group participation and salivary cortisol will significantly correlate with the subjective results of PWB, which will further confirm the physiological basis for the effects of these interventions.

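### The sample-size figures do not agree with each other: the stated inputs give 20 per group rather than 25, 90 recruited less 20% leaves 24, and the printed SD formula is not the pooled SD it is said to be

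*Protocol article*

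**What the plan says.** The Sample Size section of the protocol article bases the calculation on a loneliness effect from a cited study, d = 0.92, chosen as the smallest of three available effects (happiness 2.66, relaxation 2.32). It defines d from an intervention mean and a control mean. It prints σ as √(SD1² + SD2²)/2, with the division by 2 outside the root, and explains: "The term σ represents the pooled SD, calculated under the assumption that the two groups have equal sample sizes". It then says that "the sample size was determined based on an effect size of 0.92, a power of 0.80, and an α level of .05", read from a power chart. The result is given as: "The analysis indicated that a minimum of 25 participants per group would be required. This study will recruit 90 individuals", to allow for 20% dropout. That is 30 per arm, 10 per arm at each of three centers.

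Statistical Methods plans pairwise independent-sample t tests of each active arm against control, and of the combined arm (B) against the art-only arm (A). The source means and SDs are not given, and no multiplicity adjustment or ANOVA is mentioned.

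**The concern.** A reader who puts the stated d, power and α into a standard two-sample calculation does not get 25. Taking 20% off 90 does not give 25 per group either. The printed σ also cannot be a pooled SD: if both groups have SD s, it returns 0.707s.

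The first two discrepancies make it impossible to tell what was calculated. The third could matter more, because the text says that this σ was used to obtain d. If that was done with the printed form, the effect size behind the whole calculation is too large, and the trial falls short of the 80% power it planned for. The results will be read against that planning figure, so it should be possible to reconstruct it.

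**Working it through.** **Inputs.** From Sample Size: d = 0.92, "a power of 0.80", "an α level of .05", 25 per group, 90 in total, 20% dropout. From Statistical Methods: independent-sample t tests between arms. Sidedness is not stated for the power calculation. The within-group tests are two-sided ("2-tailed paired-sample *t* tests will be used for intragroup comparison"), so two-sided is assumed here, with one-sided shown as well.

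**Step 1: n per group at d = 0.92.**
- Normal approximation: n = 2(1.960 + 0.842)²/d² = 15.70/0.8464 = 18.5, so 19.
- Exact noncentral t: 19.55, so 20. One-sided: 15.33, so 16.
- The stated 25 is not reproduced. At 25 per group, the effect detectable with 80% power is d = 0.81.

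Only inputs that the section does not state come near 25:

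| Unstated input | n per group |
|---|---|
| Power 0.90 | 25 (normal), 26 (t) |
| α/3 | 25 (normal), 27 (t) |
| d = 0.80 | 25 (normal), 26 (t) |
| Three-group ANOVA, third mean midway | 24 |
| Dropout already included, 20/0.8 | 25 |

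If the last of these was done, the step from 25 to 30 allows for dropout a second time.

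**Step 2: dropout.**
- The plan's figure reproduces as 75 × 1.2 = 90.
- Keeping 25 evaluable after 20% loss needs 25/0.8 = 31.25, so 32 per group (96 in total), or 75/0.8 = 93.75, so 94, if inflated as one total.
- In the other direction, 90 × 0.8 = 72, or 24 per group.
- Thirty per group stays at or above 25 only up to a loss of 1 − 25/30 = 16.7%.

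**Step 3: the SD formula.**
- Equal-n pooled SD: √((SD1² + SD2²)/2).
- Printed: √(SD1² + SD2²)/2 = √((SD1² + SD2²)/4).
- Ratio of printed to pooled: √(1/2) = 0.707, for any SD1 and SD2. A d computed with the printed form is therefore √2 = 1.414 times too large.
- If 0.92 came from it, the correct d is 0.92/1.414 = 0.65. The n for 80% power is then 38.08 by exact t, so 39 per group.

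**Step 4: power under each reading (exact two-sided t, α = .05).**

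| n per group | d = 0.92 | d = 0.65 |
|---|---|---|
| 20 | 0.81 | 0.52 |
| 24 | 0.88 | 0.60 |
| 25 | 0.89 | 0.62 |
| 30 | 0.94 | 0.70 |

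**Step 5: B versus A (secondary).** With 24 per arm, the difference detectable with 80% power is 0.83 SD.

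**The case against.** The strongest reply is that, at the stated effect size, none of this does harm. A coarse power chart can easily yield a rounded-up 25, and recruiting more than 20 errs on the safe side. If 20 suffice, 24 after dropout is enough. The pilot lost 1 of 20 (5%), well inside the 16.7% that 30 per arm can absorb. This stands: the shortfall is one participant per arm and does not threaten 80% power at d = 0.92. It does not make the stated inputs, minimum and total agree.

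The second reply concerns the formula. A reader might infer that d was in fact inflated by 41%. The documents do not support that. They give no source means or SDs. The equation for d is missing from the text as extracted, so the 2 outside the root may be a typesetting or extraction slip, and the prose names the right quantity. The 0.65 branch is therefore conditional. It still needs an answer, because it separates about 88% power from about 60% at 24 per group.

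A reader might also infer that the plan claims 80% power for B versus A. It does not: d is defined as intervention against control, no sentence claims power for the active-arm contrast, and the trial calls itself exploratory. What remains is a matter of interpretation. The article says "we expect to determine the best program that is suitable for individuals who are new residents of older adult centers" by comparing the two interventions, so it would help to say what that comparison can detect.

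**Conclusion.** The Sample Size figures are wrong as written. The stated inputs require 20 per group, not 25. Recruiting 90 with 20% dropout leaves 24 per group, below the stated minimum. The printed σ is not the equal-n pooled SD. These results assume a two-sided, unadjusted two-sample t test; a one-sided test moves the required n further from 25.

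The consequence depends on one fact the documents do not give, namely how 0.92 was obtained. If it is a correct Cohen d, power for an active arm against control on loneliness is about 88% at 24 and 94% at 30 per group, and the trial is not underpowered for that contrast. If it came from the printed expression, the correct d is about 0.65, 39 per group would be needed, and power is about 60% and 70%. As it stands this is a correction to the text. It becomes a serious matter only if the recomputed d proves to be near 0.65.

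**What to change.** Before results are published, amend the Sample Size section as follows:

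1. Print the pooled SD as √((SD1² + SD2²)/2).
2. Give the source means and SDs for loneliness, and confirm d = 0.92 or recompute it.
3. State the test, sidedness and any adjustment, and replace 25 with the n per group for that d (20 if 0.92 is confirmed, 39 if it becomes 0.65).
4. State that 30 per group with 20% dropout gives 24 evaluable, and give the resulting power for an active arm against control on loneliness.
5. As a secondary clarification, say that this power does not apply to B versus A, where 24 per arm detects about 0.83 SD with 80% power.

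The cost is text only. All 90 participants are recruited and data collection has ended, so no more participants are asked for. The one risk is that the stated power becomes less favourable if d has to be revised.
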